### Data collection

Participants will go through four assessment periods at baseline, 6 weeks (post-program), 6 months, and 12 months follow-up. The training and clarification session will be completed by telephone to ensure participants are equipped with the skills to access the intervention contents. Before the first, third and fourth assessment periods, eligibility will be checked against inclusion and exclusion criteria through a telephone screening/re-screening call, 1 week prior to each visit. Participant's timeline is shown in Figure 3.

*Assessment* 1 (baseline): Clarification session about the study. If participants are still interested in enrolling in the study, eligibility will be checked, and they will be asked to fill out an informed consent form. Randomization and allocation to one of the four arms of the trial will be performed. Data on demographics and potential psychological moderators will be collected. A battery of psychological and behavioral questionnaires will be completed online using google forms (in one-week time) – running behavior (i.e. frequency and minutes per week), motivations, basic psychological needs, motives and gains, self-regulation skills, passion, flow, and vitality. This task is estimated to take approximately 1 h, but participants will be able to do breaks and return later to complete the psychometric evaluation during that week. Debrief on how to use the KOR web-based intervention content – the toolkit (approximately 1 h).

*Assessment*s 2 and 3 (intervention's end and 6-month follow-up). Email reminder prior to this evaluation period will be sent. The same battery of psychological and behavioral questionnaires will be completed online using google forms (in one-week time) – running behavior (i.e. frequency and minutes per week), motivations, basic psychological needs, motives and gains, self-regulation skills, passion, flow, and vitality –, and will take approximately 1 h.

*Assessment* 4 (12-month follow-up). Running behavior maintenance will be assessed through a telephone call, asking participants whether they keep running at their initial level or higher, or not.

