### Analytical strategy

Statistical analysis will be performed using SPSS Statistics version 25.0 (SPSS Inc., an IBM Company, Chicago IL, USA). Descriptive statistics will be calculated (mean, standard deviation and range). Repeated measures with Bonferroni corrections for adjusted comparisons will be used to examine differences between each intervention group(PNMC or SRM) and controls (i.e. free recreational runners), at all assessment points, in the primary and secondary outcomes measured. Statistical significance will be set at *p* < 0.05.

Mediation analysis, will test the psychological mechanisms underlying changes in running behavior from baseline to post program, 6 and 12 months. Multilevel modeling will be used to determine the SRM intervention effect on these motivational variables, with intervention group (SRM vs. Control group) as the between-subject factor and change in self-regulation and competence for running at baseline, 6–8 weeks, 6months and 12 months, serving as dependent variables. If necessary, multiple imputation methods will be implemented to provide robust results for primary and main secondary outcomes.

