## Discussion

This paper presents the rationale, development, study design, methods and pilot application of the KOR trial, aimed at testing the effect of the intervention on the maintenance of recreational running behavior over time, after being voluntarily initiated by community-dwelling adults in the previous 3 months. This ‘light-touch’ intervention is unique in that it approaches running behavior and its sustainability, delivered in a digital format, and based on strong theoretical foundations.

We hypothesize that the sustainability of running behaviors will be higher in the SRM groups compared to the control group. Change in running behavior (e.g. frequency and minutes of running per week) and secondary outcomes related to the quality of the running experience (e.g. passion, flow, vitality) will be used as the dependent variables.

Additionally, the results of the pilot feasibility study, intended at testing intervention adherence, participant satisfaction, and questionnaire acceptance, were also presented. Overall, the pilot study indicated that the intervention has good acceptability, feedback was very positive, but toolkit interaction decreased after the first weeks, which is common in web-based interventions (Baumel & Yom-Tov, 2018). Moreover, the generalized use of other running-related devices, applications and communities may have overlapped with the anticipated content of the toolkit, challenging participants’ interaction. The completion ratio of the post-program questionnaire was low, maybe due to its extension and burden, but also because its timeline ended near the summer break.

The main trial should reduce questionnaire length and burden, and include interface with usual monitoring gadgets and apps (APIs), to increase data detail and prevent ‘unnecessary’ data insertion by the participants. Features such as feedback and social sharing, added to the goal setting features already integrated in the toolkit, may also increase attractiveness (Hosseinpour & Terlutter, 2019).

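### The SRM multilevel model takes change scores as its outcome at baseline, where change is zero by definition, and at 12 months, where no scale is described; fitted literally with one group coefficient, it reports two thirds of the follow-up effect

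*Protocol article*

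**What the plan says.** The Analytical strategy section of the protocol article gives the mechanism model its purpose: "Multilevel modeling will be used to determine the SRM intervention effect on these motivational variables". It names one factor, "with intervention group (SRM vs. Control group) as the between-subject factor", and defines the outcomes as "change in self-regulation and competence for running at baseline, 6–8 weeks, 6months and 12 months, serving as dependent variables". It names no visit term, no group-by-visit term and no baseline covariate.

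The Data collection section sets out the visits: "Participants will go through four assessment periods at baseline, 6 weeks (post-program), 6 months, and 12 months follow-up". The questionnaire battery is completed at baseline. For the end of the intervention and the 6-month follow-up the section says "The same battery of psychological and behavioral questionnaires will be completed online using google forms (in one-week time". At 12 months it describes something different: "Running behavior maintenance will be assessed through a telephone call, asking participants whether they keep running at their initial level or higher, or not".

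A separate analysis covers the primary and secondary outcomes: "Repeated measures with Bonferroni corrections for adjusted comparisons will be used to examine differences between each intervention group".

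**The concern.** A change score needs a reference value, and the only natural one here is baseline. At baseline the change is then zero for every participant in every group, so that row carries no information on the intervention. If it stays in the outcome list and the model has a single group coefficient, that coefficient averages the real follow-up effects with a guaranteed zero.

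The sentence before it in the same section handles change correctly for running behavior: baseline is the starting point and only later visits are listed. The next sentence moves baseline into the list of outcome occasions. That is a definition stated wrongly, which differs from a detail left to a fuller document.

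The size of the SRM effect on self-regulation and competence is at stake, and the mediation question depends on it. No test result would expose the error, because estimate and standard error are scaled by the same factor.

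**Working it through.** The article gives no figure for this model, so there is nothing to reproduce.

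**Inputs from the protocol article**
- Waves with scale data: baseline, 6 weeks, 6 months, so K = 3 (Data collection).
- Effect size for psychosocial outcomes: 0.50 (Power calculations and sample size estimation), used only to set the scale.
- Participants per group: 55 (same section), used only for illustration.

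**Assumptions not in the article**
- Between-visit correlation r = 0.5, with 0.3 to 0.7 as the range.
- Unit SD, complete data, and the same effect at both follow-ups.

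**1. Scaling of the estimate.** With change scores D1 and D2 and a zero at baseline, each person's mean is (0 + D1 + D2)/3 = (2/3) × (D1 + D2)/2. In general the factor is (K − 1)/K. For K = 3, 0.50 × 2/3 = 0.333. This factor does not depend on r.

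**2. Standard error.** The variance of a person's mean follow-up change is (1 + r)/2 + 1 − 2r = 1.5 − 1.5r, which is 0.75 at r = 0.5. The SE of the group difference is √(2 × 0.75/55) = 0.165. With the zero row kept it is 0.165 × 2/3 = 0.110. The ratio of estimate to SE is the same either way: 0.333/0.110 = 0.50/0.165 ≈ 3.03.

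**3. Coverage of the true 0.50.** The bias is 0.50 − 0.333 = 0.167, which is 0.167/0.110 = 1.51 standard errors. Coverage is Φ(1.96 − 1.51) − Φ(−1.96 − 1.51) ≈ 0.67.

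**4. Simulation check** (random-intercept model, 300 replicates, 55 per group, r = 0.5, three waves)

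| Model | Estimate | SE | Coverage of 0.50 | Power |
|---|---|---|---|---|
| Pooled group effect, baseline zero row kept | 0.332 | 0.110 | 0.677 | 0.873 |
| Pooled group effect, baseline row dropped | 0.498 | 0.164 | 0.967 | 0.873 |
| Group-by-visit, baseline row kept | 0.503 (6 weeks), 0.492 (6 months) | 0.190 (6 weeks) | – | – |

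In the first row the model SE of 0.110 agrees with the empirical SD of the estimates, 0.103. In the third row the SE matches that of a plain comparison of change at that visit, 0.189.

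**5. Precision without a baseline covariate.** Adjusting the mean of the two follow-up scores for baseline gives a variance of (1 + r)/2 − r², which is 0.75 − 0.25 = 0.50 at r = 0.5. The SE is √(2 × 0.50/55) = 0.135, against 0.165 for change. The variance ratio is 0.50/0.75, a reduction of one third.

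**6. Range over r** (55 per group, formulas above)

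| r | SE, change | SE, baseline-adjusted | Coverage, zero row kept and pooled |
|---|---|---|---|
| 0.3 | 0.195 | 0.143 | 75% |
| 0.5 | 0.165 | 0.135 | 67% |
| 0.7 | 0.128 | 0.114 | 50% |

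**7. Visit lists side by side.** The outcome list has baseline, 6–8 weeks, 6 months and 12 months. The scales are described at baseline, 6 weeks and 6 months. The 12-month entry has no described scale data, and the post-program timing is worded differently in the two sections.

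**The case against.** The strongest reply is that the shrinkage belongs to a model the article does not specify. It needs three things together: change scores as rows, the baseline row kept, and one pooled group coefficient. The sentence can also be read as scores measured at each visit with their change modelled over time, and listing baseline makes sense on that reading. With a group-by-visit term the shrinkage disappears even if the zero row stays. The article condenses a fuller plan, so silence on model terms is not in itself a fault. This reply stands as far as the size of the effect goes: the loss of one third is conditional. It does not rescue the wording, because the outcome is written as change and baseline is written as an occasion.

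Second, the Assessments section classes the putative mediators as secondary outcomes, and those are also compared between groups at all assessment points by repeated measures. Routine descriptive statistics would show a variable that is zero throughout. Both points stand, and they limit the damage.

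A reader might go further than the article allows in three ways:
- **That the interval is falsely narrow.** It is not. The standard error is right for the quantity estimated. The estimate is on the wrong scale, so its interval often misses the true effect, but the test is unaffected.
- **That a loss of one quarter is equally possible.** This needs four waves of scale data, and the Data collection section describes three.
- **That the Discussion commits the trial to unadjusted change in running.** It names "Change in running behavior (e.g. frequency and minutes of running per week) and secondary outcomes" as dependent variables, but it neither says the analysis is unadjusted nor rules out a baseline covariate.

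**Conclusion.** The outcome definition is faulty as written: one listed occasion is constant by construction, and another has no described scale data. An analyst would have to guess the intended model.

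Under the literal pooled reading, the SRM effect on self-regulation and competence is reported at two thirds of its mean follow-up value. That factor is exact for three waves and a single group coefficient. The accompanying coverage of about 68% rests on a true effect of 0.50 SD, 55 per group and r = 0.5; by formula it runs from 75% at r = 0.3 to 50% at r = 0.7. P-value and power do not change. Under a group-by-visit model there is no shrinkage.

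Separately, change scores without a baseline covariate would lose precision: SE 0.165 against 0.135 at r = 0.5.

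The consequence is confined to the mechanism model. The repeated-measures comparison of primary and secondary outcomes is a different analysis and is not touched by the zero row.

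**What to change.** Reword the sentence in the Analytical strategy section so that:
- the dependent variables are the self-regulation and competence scores at the post-baseline assessments where the scales are collected, which are 6 weeks and 6 months according to the Data collection section;
- each participant's baseline score is a covariate;
- the model has group, visit and group-by-visit terms;
- the SRM effect is reported at each visit.

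Remove baseline from the list of outcome occasions. Reconcile the 12-month entry with the Data collection section, and use one wording for the post-program visit (6 weeks or 6–8 weeks).

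The same baseline-adjusted form may be used for running minutes and frequency as a gain in efficiency. That is optional and does not correct an error.

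The cost is a short change of analysis wording. No new data are needed, because the baseline scores are already collected.

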### Motivation and self-regulation intervention

We developed a web-based intervention adapted from the motivational and self-regulation arm of the NoHoW tria (Marques et al., 2020; Scott et al., 2019). It consists of 11 short sessions divided in 8 modules with motivational and self-regulation based exercises, quizzes, videos and animations aimed to elicit reflection about motives, goals, barriers and strategies to foster running behavior sustainability. Beyond the long-term promotion of running behavior, by implementing theory-based and evidence-based behavior change techniques, this brief intervention aims at promoting participants’ intrinsic and well-internalized motivations for running and the use of self-regulation skills (e.g. goal setting) that facilitate behavior maintenance.

The intervention includes:
Access to a web-based intervention comprising 11 distinct sessions of 5–10 min each and 8 educational modules concerning motivation and self-regulation constructs, delivered through several technological implementations, including videos, animations, quizzes and exercises, as well as images, text and audio (Figure 4). Several multimedia tools, including a web-based HTML5 interactive map as a navigation tool for the SRM sessions (http://leafletjs.com/), the questionnaires platform to design interactive features, and whiteboard drawings to convey some of the more theoretical constructs of the intervention (http://www.videoscribe.co/), were used to develop these implementations, supported by the team's previous experience in similar interventions.Bi-weekly text messages (see Table 1 for an overview of weekly text messages to participants) are sent to prompt participants toward the sessions and each week specific contents. Yet, participants are able to move faster or slower through the program to fit their needs and availability.

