The SRM intervention includes both motivation and self-regulation components. The intervention's theoretical logic model is adapted from the NoHoW project (Marques et al., 2020; Scott et al., 2019) and presented in Figure 1. The self-regulation skills component will seek to empower users to identify goals and make action plans for when, where, and how the goals will be implemented, allowing them to formulate explicit implementation intentions. Coping plans for relapses will also be supported. The motivational component is therefore based on SDT and configured to optimally support participants’ psychological needs for autonomy, competence, and relatedness, via specific technological implementations (e.g. self-awareness exercises, videos and practice modules), and as a result improve autonomous regulation of physical activity behaviors. Participants will explore personal motives to run, skills, life goals, social connections, and other motivational elements. Messages, videos, animations, self-awareness questionnaires, among other tools, will stimulate users’ sense of volition and ownership (vs. external pressure), confidence and competence (vs. unpreparedness and sense of failure), and positive social support (vs. isolation). It is anticipated that the use of these implementations will increase autonomous self-regulation and intrinsic motivation, which are associated with longer-term behavior change, and positive health outcomes.

The SRM web-based toolkit will be accessible only to the groups receiving the SRM intervention. In addition, all the study participants will receive weekly email messages with general technical information about running. An individual telephone session will introduce runners to specific elements of their unique intervention and how it will unfold.

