### Assessments

Data on demographics (age, gender, date of birth, education, income, employment, marital status, weight, height, physical activity history, and personal characteristics) and potential psychological moderators (i.e. index of autonomous functioning) will be collected only at baseline.

The primary outcome of this study is running behavior, which will be measured at baseline, intervention's end and 6-month follow-up by self-report (frequency and minutes of running per week). At 12 months, participants will be asked by telephone whether they keep running (at least) at their initial level, or not.

Secondary outcomes will include putative mediators and outcomes. Basic psychologic need satisfaction will be assessed via the Psychological Need Satisfaction in Exercise Scale (Wilson, Rogers, Rodgers, & Wild, 2006); Basic psychological need frustration will be assessed trough the Basic Psychological Need Frustration in Exercise Scale (Chen et al., 2015); Motives and gains via Exercise Motives and Gains Inventory (Ingledew, Markland, & Strömmer, 2014); Behavioral regulations will be assessed via the Behavioral Regulation in Exercise Questionnaire – 3 (Cid et al., 2018); Self-determination trait will be assessed via the Index of Autonomy Functioning (Weinstein, Przybylski, & Ryan, 2012); Self-regulation skills will be measured trough the Action planning, Coping planning, and Action control scales (Sniehotta, Scholz, & Schwarzer, 2005a; Sniehotta, Schwarzer, Scholz, & Schuz, 2005b); Self-efficacy will be assessed via the Modified Bandura's Exercise Self-Efficacy Scale (Bandura, 1997); Automaticity will be measured trough the Self-Report Behavioural Automaticity Index (Gardner & Tang, 2014; Gardner, Abraham, Lally, & de Bruijn, 2012); and exercise identity via the Exercise Identity Scale (Anderson & Cychosz, 1994). Regarding psychological outcomes, flow will be measured through the Dispositional Flow Scale – 2 in Exercise (Jackson & Eklund, 2002); Vitality will be assessed through the Subjective Vitality Scale (Ryan & Frederick, 1997); and passion through the Passion Scale (Cid et al., 2019).

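### The multilevel model of the SRM effect omits autonomous/intrinsic motivation, a stated SRM target, and lists two time points that give no usable change score

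*Protocol article*

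**What the plan says.** All references are to the Protocol article.

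- **Aim of SRM** (Motivation and self-regulation intervention): "this brief intervention aims at promoting participants’ intrinsic and well-internalized motivations for running and the use of self-regulation skills".
- **Components and mechanism** (same section, text after Table 1): "The SRM intervention includes both motivation and self-regulation components". The motivational component is meant to support autonomy, competence and relatedness and thereby improve autonomous regulation. The tools are expected to "increase autonomous self-regulation and intrinsic motivation, which are associated with longer-term behavior change".
- **Measurement** (Assessments): "Behavioral regulations will be assessed via the Behavioral Regulation in Exercise Questionnaire – 3". Need satisfaction has its own scale, and self-regulation skills are measured by action planning, coping planning and action control scales. Putative mediators are classed among the secondary outcomes.
- **Timing** (Data collection): the questionnaire battery, including motivations, needs and self-regulation skills, is completed at baseline, at the end of the intervention (6 weeks) and at 6 months. The 12-month assessment is a telephone call asking whether running continues at the initial level or above.
- **Analysis** (Analytical strategy): "Multilevel modeling will be used to determine the SRM intervention effect on these motivational variables", comparing SRM with control, with "change in self-regulation and competence for running at baseline, 6–8 weeks, 6months and 12 months, serving as dependent variables". The same section also plans a repeated-measures comparison on all primary and secondary outcomes, and a mediation analysis of psychological mechanisms that names no mediator.

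**The concern.** The mechanism in the intervention section has two strands, and the scales for both are collected. The model introduced to estimate the SRM effect on motivational variables then fixes its outcomes as self-regulation and competence. The phrase about these motivational variables has no list before it, so the two constructs that follow are the only definition the reader gets. Neither is the autonomous or intrinsic motivation that the motivational component is meant to raise, at least on the plain reading of self-regulation as the skills scales.

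What is at stake is whether the trial says in advance how it will test the motivational half of its theory. With many psychological scales collected, an outcome list that does not match the stated mechanism leaves room to choose mediators after the results are known. The outcome definition also refers to times at which no informative change score exists, so the model cannot be fitted as written.

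**Working it through.** The plan states no figure to reproduce on this point. The check sets the sections side by side.

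**1. Stated mechanism against modelled outcomes**

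| Construct | Stated SRM target or pathway? | Scale collected at baseline, 6 weeks and 6 months? | Named in the multilevel model? |
|---|---|---|---|
| Autonomous/intrinsic motivation | Yes, target | Yes, BREQ-3 | No |
| Self-regulation skills | Yes, target | Yes, planning and action control scales | Yes, as self-regulation |
| Competence | Yes, need supported | Yes, need satisfaction scale | Yes |
| Autonomy | Yes, need supported | Yes, need satisfaction scale | No |
| Relatedness | Yes, need supported | Yes, need satisfaction scale | No |

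The model covers the self-regulation strand. It covers the motivational strand through one of three needs, and it does not reach the end point of that strand.

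**2. Does the term self-regulation already include autonomous motivation?** The intervention section speaks of autonomous self-regulation as a motivational result. The Assessments section uses self-regulation skills for the planning and action control scales. The analysis sentence says only self-regulation. If the skills scales are meant, autonomous motivation is missing. If the BREQ-3 is meant, the sentence does not say so, and the skills scales are then missing. Either way the sentence has to name its scales.

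**3. Is the construct covered elsewhere?** Yes. The BREQ-3 is listed under secondary outcomes, and the repeated-measures comparison takes in all secondary outcomes. The mediation sentence is general. The omission is therefore from this model and not from the whole plan.

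**4. Time points.** Let Y(t) be a scale score at time t and the change be D(t) = Y(t) − Y(0).

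- Baseline: D(0) = Y(0) − Y(0) = 0 for every participant, so there is no outcome to model.
- First post-baseline visit: given as 6–8 weeks here, but as 6 weeks in Study design and Data collection. Scales are collected.
- 6 months: scales are collected.
- 12 months: only the telephone question on running is described, so Y(12 months) is not available for these scales.

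Usable times are 4 − 1 (baseline) − 1 (12 months) = 2, namely 6 weeks and 6 months.

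**The case against.** The strongest reply is that the plan does analyse autonomous motivation. The repeated-measures comparison includes it, and Study design names free runners with SRM against free runners without it as the comparison for motivational and other psychological variables, with randomisation within that stratum. Self-regulation skills are a joint target in their own right, and the Background calls such skills important mediators. Competence belongs to the pathway by which autonomous motivation is fostered. A condensed article may leave the full mediator list to the analysis plan, and change at baseline may simply be a loose list of visits.

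Most of this stands, and it limits the point. A reader might infer that the hypothesised mediator has been dropped from the trial, that the two modelled constructs are peripheral, or that the results could not bear on the theory either way. The documents support none of these, given the repeated-measures coverage, the open mediation sentence and the equal standing of self-regulation skills. Nor can the loss be put as a proportion of the indirect effect, because the article gives no correlations among the constructs.

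Two parts of the reply do not stand. First, the article does not leave the model's outcomes open for a later document. It fixes a list, and that list does not match the intervention section. Second, even if the baseline entry is loose wording, the 12-month entry conflicts with the described data collection, so the sentence needs correcting in any case.

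**Conclusion.** The concern holds for one model. The only analysis dedicated to the SRM effect on mediators names self-regulation and competence and omits autonomous/intrinsic motivation, one of the two mechanisms SRM targets, although its scale is collected at three assessments. The motivational half is tested there only through one of three needs. Two of the four listed time points cannot supply a usable change score as the data collection is described.

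The size is modest. The primary comparison is untouched, autonomous motivation remains a secondary outcome in the repeated-measures comparison, and the mediation analysis could still include it. What is lost is a clear advance statement of which mediators the mechanism model will test, and when.

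This rests on two readings: that self-regulation in the analysis sentence means the skills scales (the other reading needs the same clarification), and that the Assessments and Data collection sections describe the 12-month assessment completely.

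**What to change.** Rewrite the multilevel sentence in Analytical strategy so that it:

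1. names as dependent variables and candidate mediators autonomous motivation (the autonomous/intrinsic BREQ-3 subscales), need satisfaction (autonomy, competence, relatedness) and self-regulation skills, each tied to its scale in Assessments;
2. models the post-baseline scores with the baseline score as covariate, in place of a change score that includes baseline;
3. limits the time points to 6 weeks and 6 months, and uses one label for the first visit throughout. If psychological scores at 12 months are intended, Assessments and Data collection must say that they are collected.

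The scales are already in the battery, so no data collection is added. The cost is a few more secondary tests: counting self-regulation skills and autonomous motivation as one construct each, the list grows from 2 constructs to 1 + 3 + 1 = 5. They should be reported as secondary.

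### The analysis uses self-regulation, competence and change in running at 12 months, but the 12-month assessment collects only a yes/no telephone answer

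*Protocol article*

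**What the plan says.** **What is collected.** Under Assessments, the primary outcome is running behavior, taken at baseline, at the end of the intervention and at "6-month follow-up by self-report (frequency and minutes of running per week". The same paragraph then changes the measure: "At 12 months, participants will be asked by telephone whether they keep running (at least) at their initial level, or not".

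The Data collection section gives the same schedule. At baseline, participants complete an online set of questionnaires covering running frequency and minutes, psychological needs, self-regulation skills and other scales. For Assessments 2 and 3 (intervention's end and 6 months), "The same battery of psychological and behavioral questionnaires will be completed online using google forms (in one-week time". For Assessment 4, at 12 months, the article lists only the call: "Running behavior maintenance will be assessed through a telephone call, asking participants whether they keep running at their initial level or higher, or not".

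**What is analysed.** The Analytical strategy section names 12 months in two sentences and implies it in a third:

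- The multilevel model of the SRM effect takes change in self-regulation and competence as its outcome, at baseline, 6–8 weeks, "6months and 12 months, serving as dependent variables".
- "Mediation analysis, will test the psychological mechanisms underlying changes in running behavior from baseline to post program, 6 and 12 months".
- Repeated-measures comparisons will "examine differences between each intervention group(PNMC or SRM) and controls (i.e. free recreational runners), at all assessment points", for the primary and secondary outcomes.

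The Discussion gives frequency and minutes per week as examples of the change in running that will serve as a dependent variable.

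**The concern.** The schedule and the analysis text cannot both be followed. Two sections agree that no psychological scale and no running quantity is recorded at 12 months. A third section analyses such variables at that time.

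The trial is about maintaining running, lasts one year, and has its last assessment at 12 months. If the conflict is found only at analysis, the 12-month values cannot be recovered. The team would then have to drop the planned 12-month models or replace them with something chosen after the data are in. The yes/no answer is also on a different scale from the earlier measurements. Someone who has greatly increased their running and someone who has stayed level both answer yes. Someone who has stopped and someone who has slipped slightly both answer no.

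**Working it through.** The plan states no figure that bears on this point, so there is none to reproduce. The check sets the measurement schedule (Assessments; Data collection) against the time points that the Analytical strategy section requires. I take its 6–8 weeks to be Assessment 2, scheduled at 6 weeks.

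| Variable | Baseline | 6 weeks | 6 months | 12 months | Occasions the analysis names |
|---|---|---|---|---|---|
| Self-regulation, competence | scale | scale | scale | not collected | all 4 |
| Running frequency and minutes | self-report | self-report | self-report | not collected | change from baseline to each of the 3 later occasions (as running behavior) |
| Running at initial level or above | – | – | – | yes/no by telephone | not named separately |

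1. **Multilevel model.** The scales exist at 3 of the 4 occasions named. At 12 months the values are absent for every participant, so no 12-month effect on these variables can be estimated.

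2. **Multiple imputation.** The article allows this if necessary. It works by learning, from participants who have a value, how that value relates to the rest of the data. Here nobody has a 12-month value, so the data say nothing about its distribution or its relation to treatment arm. Any imputed figure would be pure assumption.

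3. **Change in running to 12 months.** A change in minutes or frequency is the 12-month value minus the baseline value. The baseline value is recorded and the 12-month value is not, so the difference cannot be formed. What exists is the yes/no answer, a coarse indicator of change from the initial level. A mediation model with that answer as a binary outcome, and mediators from 6 weeks or 6 months, could be fitted. The sentence on mediation does not describe one; it treats the three follow-up times alike.

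4. **Repeated measures.** The comparison of weekly minutes has 3 quantitative occasions out of 4. A yes/no answer cannot be a fourth level of a within-person factor whose other levels are minutes per week.

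5. **Up to 6 months.** Every variable named in these analyses is collected at baseline, 6 weeks and 6 months. Those analyses can be run as written on this account.

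The timeline figure is not reproduced in the text available. The Assessments and Data collection sections are explicit and agree, so the result does not depend on it.

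**The case against.** The best case for the plan is that only one part is truly impossible: one time point of a secondary, mechanistic model. The mediation sentence speaks of running behavior, not minutes, and the telephone item is introduced in the paragraph that defines that outcome. The Discussion offers minutes and frequency only as examples. The repeated-measures sentence refers to outcomes measured, which can be read as each outcome at the times it was taken. A condensed article may also leave the model for a yes/no item to the full protocol or analysis plan.

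Much of this stands. The repeated-measures sentence is weak evidence by itself. Mediation of the yes/no answer by earlier mediators is feasible. The absence of a stated model for that answer is not an error in an article of this kind. But the multilevel sentence names 12 months for scales that are not given then, and no later document can analyse data that were never collected. That is a contradiction between stated passages, not a missing detail.

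A reader might infer three further things that the documents do not support:

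- **That no 12-month analysis is possible.** This is too broad, for the reasons above.
- **That the 12-month answer is biased by recall in participants who know their arm.** The article confirms that there is no blinding. It does not say whether the caller states the baseline level, which is on file from Assessment 1. The self-reported minutes are unblinded too.
- **That the yes/no item leaves the trial underpowered.** The sample size is based on running minutes and psychosocial variables, not this item. Any power figure would need an assumed maintenance rate that the article does not give, and it would have no bearing on the mismatch.

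**Conclusion.** The contradiction is real and explicit. At 12 months, 100% of the self-regulation and competence values required by the multilevel model are missing by design, so that analysis cannot be run. Change in running minutes or frequency to 12 months cannot be computed, and the yes/no answer cannot join the repeated-measures comparison of weekly minutes. Mediation to 12 months is possible only as a binary-outcome model with earlier mediators, and the plan does not set one out.

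The comparisons at 6 weeks and 6 months, including those on the quantitative primary outcome, are not touched. This should be fixed, but it is not a fault that undermines the trial. The conclusion assumes only that the schedule stated twice in the article is the one in force.

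**What to change.** - **Psychological variables:** end the multilevel model at 6 months by removing 12 months from that sentence.
- **12-month call:** add the two baseline items, runs per week and minutes per week. Running can then be analysed at all four occasions on the scale of the primary outcome.
- **Maintenance at 12 months:** derive it by comparing the reported values with the recorded baseline, stating beforehand whether runs, minutes or both must be at or above that level. Analyse it by logistic regression on randomised arm, adjusted for stratum (PNMC or FRR) and baseline running.
- **Mediation:** use mediators measured at 6 weeks (or 6 months) and running at a later time point, so that the mediator precedes the outcome. Name the model for each outcome scale.
- **Repeated measures:** list the occasions that apply to each outcome.

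The cost is two more questions in a call already planned, and revised analysis wording. The new questions must be in place before the first 12-month calls. If they cannot be added, analyses of minutes and frequency should end at 6 months, with the yes/no answer analysed at 12 months as a binary outcome.
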